## Abstract

Post-acute sequelae of SARS-COV-2 (PASC) is growing in prevalence, and involves symptoms originating from the central neurological, cardiovascular, respiratory, gastrointestinal, autonomic nervous, or immune systems. There are non-specific symptoms such as fatigue, headaches, and brain fog, which cannot be ascribed to a single system. PASC places a notable strain on our healthcare system, which is already laden with a large number of acute-COVID-19 patients. Furthermore, it impedes social, academic and vocational functioning, and impacts family life, relationships, and work/financial life. The treatment for PASC needs to target this non-specific etiology and wide-ranging sequelae. In conditions similar to PASC, such as “chemo brain,” and prolonged symptoms of concussion, the non-specific symptoms have shown to be effectively managed through *education and strategies for self-management* and *Mindfulness* interventions. However, such interventions have yet to be empirically evaluated in PASC to our knowledge. In response to this gap, we have developed a virtual education intervention synthesized by psychiatrists and clinical psychologists for the current study. We will undertake a two-phase randomized controlled trial to determine the feasibility (Phase 1; *N* = 90) and efficacy (Phase 2; sample sized based on phase 1 results) of the novel 8 week Education and Self-Management Strategies group compared to a mindfulness skills program, both delivered virtually. Main outcomes include confidence/ability to self-manage symptoms, quality of life, and healthcare utilization. This study stands to mitigate the deleterious intrusiveness of symptoms on everyday life in patients with PASC, and may also help to reduce the impact of PASC on the healthcare system.

**Clinical trial registration:**https://classic.clinicaltrials.gov/ct2/show/NCT05268523; identifier NCT05268523.

## Introduction

### Long-COVID: diagnosis and epidemiology

The coronavirus disease 2019 (COVID-19) is caused by the severe acute respiratory syndrome coronavirus 2 (SARS-CoV-2) (1). While the word “acute” implies a brief illness (2), many patients experience persisting symptoms (3). These ongoing and sometimes debilitating symptoms were initially brought to public attention by online social support groups that quickly proliferated early in the pandemic (4); these groups coined the terms “Long-Hauler and ‘Long-COVID.” Since then, prolonged symptoms have been additionally referred to as *post-COVID syndrome*, *long-haul COVID-19*, and *post-acute sequelae of SARS-COV-2* (PASC) (4). The labels initially referred to patients with symptoms lasting more than one month following diagnosis of SARS-CoV-2 (5–8), and now typically refer to symptoms lasting three or more months (9–11). Here, we use the term PASC because it is explicit in its focus on long-lasting symptoms of COVID-19 without etiological assumptions of symptoms.

Like the acute illness, enduring symptoms of COVID-19 are often multi-faceted (12–15). Origins of symptoms may be central neurological (e.g., cognitive impairment, depression/anxiety, loss of sense of smell/taste) (14, 16), cardiovascular (e.g., chest pain/tightness, tachycardia) (17, 18), respiratory (e.g., dyspnea, cough) (14, 19–23), gastrointestinal (e.g., nausea, abdominal pain, altered gut microbiota) (24–26) and/or musculoskeletal (e.g., joint/muscle pain) (27). Symptoms may also have their origins in the autonomic nervous (28) or immune systems (inflammatory and neuroinflammatory) (29). While some symptoms can be ascribed to specific etiology, there are also symptoms where the pathophysiology and causes are uncertain (30).

The exact prevalence of PASC remains uncertain, but given the vast numbers of patients sustaining SARS-CoV-2 – nearly 500 million at the time of writing (31) – even the smallest estimates are concerning, especially as protracted sequelae occur even in mild acute illness and in young and fit patients. One of the largest meta-analyzes to date, pooling 54 studies and almost 1.2 million patients’ data from around the world, found that 6.2% of patients experienced symptoms lasting beyond 4 weeks (32). Other smaller-scale studies have reported prevalence rates varying between 10 and 65% (33–35).

Not surprisingly, the societal impact of PASC is significant. For instance, SARS-CoV-2 is estimated to share a similar mortality rate to that of seasonal influenza, causing an estimated doubling proportion of deaths annually (36). Moreover, the increased healthcare utilization places a notable strain on a system already burdened by large numbers of patients and healthcare workers with acute COVID-19 (28, 37). A retrospective cohort study in Canada found that the mean days in hospital per-person-year increased by 47–53%, 8 weeks or more after a COVID-19 infection (38). Moreover, the array of cognitive, physical and emotional sequelae of PASC impede social, academic and vocational functioning with deleterious financial consequences (39). A large-scale survey of >3,000 patients with PASC (40) found 71% of respondents endorsing compromise to family life and relationships, with 31% endorsing reduced ability to care for children and dependents. Work-related impacts were endorsed by 81% of people, and 36% endorsed financial impact. Similarly, Davis and colleagues (14) in a survey of 3,762 participants with PASC found that 45% needed a reduced work schedule, and 22% were not working due to illness at 6 months post-diagnosis.

Given the above consequences, a treatment for PASC is needed to reduce its burden on patients and society. However, the wide-ranging non-specific and specific nature of symptoms has made this a significant treatment challenge (41).

### Identifying treatment options: overlap of PASC with related disorders

One path for treating PASC is to identify other disorders with an overlapping clinical presentation that have treatments with demonstrated efficacy (42). PASC shares a likeness with several conditions in which a discrete organic event is followed by a cluster of prolonged and non-specific symptoms. These include “chemo brain” (43–47), post-viral syndromes such as post influenza, SARS (48), Middle East Respiratory Syndrome (49), myalgic encephalomyelitis/chronic fatigue syndromes (50), and the prolonged symptoms of concussion (51). In all of these disorders, symptoms can include fatigue, sleep disturbance, brain fog, headache and mood disturbance, for example, which are some of the more common non-specific PASC sequelae.

Of particular relevance to PASC is the idea of symptom interplay and exacerbation. This has been described in the concussion literature from a “network perspective,” whereby non-specific symptoms amplify and reinforce one another (52). For example, fatigue may cause or exacerbate cognitive symptoms, which may cause or escalate mood symptoms, which may in turn worsen sleep (53).

The diagnostic challenges of non-specific and trans-diagnostic symptoms in post-viral syndromes, chemo brain and prolonged symptoms of concussion have led to treatment approaches that do not necessitate a mapping between symptom and cause at the individual patient level. One such approach is *education and strategies for symptom self-management* (e.g., educating about the disorder and expectations regarding symptom recovery; providing strategies for managing one’s own symptoms), which has shown efficacy for managing non-specific and specific symptoms associated with post-viral syndromes, and chemo-brain (54). Education has also been found to be prophylactic against the development of prolonged symptoms of concussion (55). Not surprisingly, education and strategies have been advocated for managing prolonged COVID-19 symptoms (56), but remain to be empirically tested in this population. Another approach with efficacy for non-specific and specific symptoms is *Mindfulness* (referring to increasing one’s awareness of the present moment) (57), and which can enhance an individual’s internal locus of control for optimizing health (58). Mindfulness treatments have been shown to improve: fatigue in patients with cancer (59–61); anxiety, depression and quality of life in patients with myalgic encephalomyelitis/chronic fatigue syndromes (62); chronic pain, depression relapse, addiction (57); and, symptoms of fatigue and depression in concussion (54, 63). Mindfulness interventions have also shown to improve prolonged symptoms of concussion (63–65). In the context of PASC, however, Mindfulness has limitations for certain physical symptoms such as shortness of breath, lung function, or exercise intolerance (66).

### Limited research into current approaches to treatment of PASC

While a number of clinical recommendations have been made for PASC patients, there is a paucity of treatment research to date. The recommended pharmacological approach is symptom-based; this has mainly included the repurposing of drugs that are employed for similar conditions and symptoms (5, 67). For example, medications for chemotherapy and brain fog [e.g., methylphenidate, donepezil, modafinil, and memantine (68)] are under consideration for brain fog in PASC (69). However, currently, no drugs have been found to effectively target subjective cognitive symptoms of PASC, and studies investigating their efficacy are still limited to case-studies (70).

A number of recommendations have been made to promote self-education and strategy use. The National Institute for Health and Care Excellence (NICE) guidelines recommend directing patients to online resources and apps to optimize self-management, for example referring to behavioral guidelines published by the WHO (71) and a PASC self-management web-page created by the Provincial Health Services Authority in Canada (72). As well, a recent guide published for primary care physicians advocated educating patients with PASC with concrete strategies and recommendations for managing their respiratory, cognitive, neurological, and somatic symptoms (73). To date, there are no published multidisciplinary education, strategy and self-management approaches for PASC.

### Aims and hypotheses

In sum, while management of acute COVID is being studied extensively, there is no candidate treatment that targets, let alone alleviates, all or most symptoms of PASC across patients. In response to this gap in care, we developed an education and strategies intervention inspired by findings in related populations that have shown efficacy. This intervention synthesized by psychiatrists and clinical psychologists provides practical recommendations to manage both the specific and non-specific symptoms of PASC. The current study aims to (i) demonstrate the feasibility and efficacy of a novel education and strategies intervention for self-management of PASC symptoms that can be delivered cost-effectively, (ii) and to disseminate an intervention package to aid symptom self-management free-of-charge to licensed therapists for delivery to their patients with PASC. The intervention package will be fully manualized, with (i) videos of presentations from clinician-scientists (cardiology, neurology, respirology, rheumatology, psychology) with experience in PASC that includes frequently asked questions from patients and answers from clinicians; and (ii) PowerPoint presentations plus scripts to be delivered by the facilitator.

The treatment under development employs remote delivery, which has shown to be cost-effective (74, 75), and can tackle the scale and geographic distance of patients from treatment centers. Remote delivery also prevents infection risk, employing a group-based approach which has shown to be cost-effective (76), and may be psychologically optimal given the proliferation of online groups for individuals with PASC, suggesting a need for mutual support. Importantly, group-based approaches for related disorders have been proven effective and feasible (77) as have telerehabilitation and education approaches (78).

We will undertake a two-phase randomized controlled trial (RCT) to determine feasibility and effect size (Phase 1) and efficacy (Phase 2) for a novel 8-week Education and Self-Management Strategies group compared to a mindfulness skills program. Phase 2 is a full-scale quantitative-only RCT, with refinements and power analysis based on Phase 1 results, and an additional third no-treatment control arm. Outcomes of interest include confidence and ability to self-manage symptoms, quality of life, healthcare utilization. Hypotheses: Both interventions will be associated with enhanced mood, anxiety, quality of life and management of dyspnea symptoms. The education and self-management strategies program will additionally increase confidence to self-manage symptoms, decrease intrusiveness of Long-COVID symptoms in everyday life, and decrease medical visits, more so than the mindfulness group.

## Methods

### Participants

Individuals (*N* = 90; >18 years) with previously diagnosed COVID-19 and experiencing symptoms lasting for more than 3 months (i.e., persisting symptoms) are currently being recruited for Phase 1. Sample size is based on paired tests from our prior concussion study (79) (*N* = 61; under review) that used the same primary outcome. With effect size 0.59 and standard alpha and beta values, 26 pairs are needed. Factoring (i) 20% attrition (conservative given 7% attrition in a similar concussion study [79; under review] and 9% in the pilot group for the present study), and (ii) a further 25% for 1-month follow-up, we will recruit N = 45 for education of self-management strategies group and N = 45 for mindfulness skills group. Key inclusion criteria are: positive COVID-19 diagnosis a minimum of 3 months prior to study participation; proof of COVID-19 diagnosis through PCR, rapid antigen or serology test; self-report experiencing 3 or more persisting symptoms from 2 or more categories of mood, cognitive and somatic domains; age > 18; and English speaking. Key exclusion criteria include past acute ventilator support; past or present major neurological/psychiatric conditions including dementia, mild cognitive impairment, psychotic illness, mania, chronic fatigue syndrome, fibromyalgia, chronic Lyme disease, and/or traumatic brain injury.

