#### Efficacy analyzes

To assess pre-to post-treatment and follow-up changes for the primary outcome (PMCSMS), we will undertake repeated measures group (Education vs. Mindfulness) by time (pre-, post-, and follow-up-education/mindfulness/waitlist group). ANCOVAs controlling for acute COVID-19 severity and time post-diagnosis. Secondary outcomes will also be examined in the same manner.

Hierarchical regression analyzes will be performed to examine impact of potential moderator variables on pre-to-post treatment improvement on the PMCSMS. In the first block, the moderators will be age, acute COVID severity, and time-post diagnosis. Sex and gender will be included in the second block, and Brief COPE, AIIR and MHLC will be added in the final block. Analyzes of repeated measures data will be performed using the Mixed Models for Repeated Measures (MMRM) methodology (96). We will employ a comparison of bias-corrected covariance estimators for MMRM analysis in longitudinal data with dropouts in order to accommodate the possibility of missing assessments or of assessments at different times post-diagnoses and to provide an effective framework for hierarchical regression analyzes and further exploratory analyzes (96).

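### The 45 per arm comes from a paired, within-arm calculation, so the stated power does not carry over to the planned Education versus Mindfulness comparison

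*Protocol article*

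**What the plan says.** The sample-size paragraph (Methods, Participants) opens with "Sample size is based on paired tests from our prior concussion study" and continues: "With effect size 0.59 and standard alpha and beta values, 26 pairs are needed". It then allows for "20% attrition (conservative given 7% attrition in a similar concussion study", where 9% is also quoted for this study's own pilot group, and for "a further 25% for 1-month follow-up". It ends: "we will recruit N = 45 for education of self-management strategies group and N = 45 for mindfulness skills group".

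Study design describes Phase 1 as a randomised, parallel, two-arm trial with 1:1 allocation. For the primary outcome, the Perceived Medical Condition Self-Management Scale (PMCSMS), Efficacy analyzes states: "we will undertake repeated measures group (Education vs. Mindfulness) by time". Aims and hypotheses expects Education to do better than Mindfulness on confidence to self-manage and on symptom intrusiveness, and to "decrease medical visits, more so than the mindfulness group".

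The same section gives Phase 1 the task of establishing feasibility and effect size, and leaves efficacy to Phase 2. Aims and hypotheses and Study design both say that Phase 2 will have its own power analysis, based on Phase 1 results. Ethics and dissemination makes the larger trial conditional on seeing preliminary efficacy in Phase 1.

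**The concern.** A paired calculation gives the number of people needed to detect a change from baseline within one group. Here that number becomes the size of each arm in a trial whose primary-outcome analysis compares two groups. With equal SDs of change in the arms, the difference between two independent mean changes has twice the variance of one mean change. At the same standardised effect, each arm therefore needs nearly twice as many people. The effect also has a different meaning: between arms, it is the Education change minus the Mindfulness change.

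The paragraph is the only sample-size justification in the article, and it appeals to "standard alpha and beta values" without saying which comparison they cover. What is at stake is how a null result would be read. If the group-by-time test is non-significant at 55% to 79% power, or less, that says little about whether Education is better. It could still be taken as absence of the preliminary efficacy on which the larger trial depends.

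**Working it through.** **Inputs from the article.** Effect size 0.59; 26 pairs; 20% attrition; a further 25% to the 1-month follow-up; 45 recruited per arm; 9% attrition in the pilot group.

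**Assumptions.** Alpha, sidedness and power are not given as numbers. I take two-sided 0.05 and 80%. I read 0.59 as mean change divided by the SD of change, with the same SD in both arms.

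**Step 1: reproduce the plan's figure.** For a paired t-test the noncentrality is 0.59 × √n.
- n = 25 gives 80.8% power and n = 26 gives 82.4%, so 25 pairs suffice and the stated 26 is reproduced to within one.
- Inflation: 26 / 0.80 / 0.75 = 43.3, so 44 per arm, against 45 recruited.

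The plan's arithmetic is sound for a paired test. It confirms that 45 per arm is the within-arm number applied to each arm.

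**Step 2: evaluable numbers per arm.**
- After 20% loss: 45 × 0.80 = 36.
- After both losses: 45 × 0.80 × 0.75 = 27.
- After 9% loss: 45 × 0.91 = 40.95, about 41.

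**Step 3: power of the between-arm comparison.** For a two-sample t-test on change scores the noncentrality is d × √(n/2), with 2n − 2 degrees of freedom. Set d = 0.59, which requires zero mean PMCSMS change under Mindfulness.

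| Evaluable per arm | Situation | Noncentrality | Power |
|---|---|---|---|
| 26 | number treated as sufficient | 2.13 | 55% |
| 27 | both planned losses (1 month) | 2.17 | 57% |
| 36 | 20% loss (week 8) | 2.50 | about 70% |
| 41 | 9% loss (week 8) | 2.67 | 75% |
| 45 | no loss | 2.80 | 79% |

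**Step 4: number needed.** At d = 0.59, 46 per arm falls just short of 80% and 47 reaches it. With the plan's own losses, 47 / 0.80 / 0.75 = 78.3, so 79 per arm or 158 in total.

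**Step 5: minimum detectable difference at 80% power.** It is 0.67 SD of change at 36 per arm and 0.78 SD at 27 per arm. Both exceed 0.59.

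**Step 6: sensitivity.**
- One-sided 5% with 90% power gives 27 pairs, also close to the stated 26. The between-arm need is then 50 evaluable per arm, so the conclusion is unchanged.
- If Mindfulness also raises PMCSMS, the difference is smaller than 0.59. As an illustration only, d = 0.4 gives 39% power at 36 per arm. The article does not supply that value.
- If baseline PMCSMS were adjusted for, with an assumed pre-post correlation of 0.3 to 0.7 and no Mindfulness change, power would be 76% to 87% at 36 per arm and 64% to 75% at 27 per arm. The covariates listed in Efficacy analyzes are acute severity and time since diagnosis, not baseline PMCSMS.

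**The case against.** The strongest reply is that Phase 1 is a pilot. The article gives it feasibility and effect size, leaves efficacy to Phase 2, and promises Phase 2 a separate power analysis. A pilot with 57% or 70% power for a between-arm contrast is not defective for that reason alone. This stands, and it limits the severity. It does not remove the point: Phase 1 was sized on an effect size with alpha and beta, it has a named primary efficacy outcome, and that outcome is analysed between arms.

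A reader might infer that the article claims conventional power for Education versus Mindfulness. It does not. The paired basis is stated openly and no between-arm power is given.

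A reader might also infer that the protocol expects Mindfulness to improve the primary outcome, so that 0.59 is contradicted by its own hypotheses. The text does not go that far. The benefits expected of both programmes are mood, anxiety, quality of life and dyspnoea management. Confidence to self-manage is listed among the things Education should improve more. That allows some Mindfulness gain on PMCSMS without predicting one, so very low power figures based on a halved effect would rest on the reader's own assumption.

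Nor does Ethics and dissemination define preliminary efficacy as a significant between-arm test. A within-arm gain is an equally open reading.

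Finally, the exact powers are conditional. The 20% attrition is described as conservative, the mixed model can use partial follow-up, and baseline adjustment would help. This supports quoting a range rather than a single figure.

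**Conclusion.** The point holds as a mismatch between the test that was sized and the test that is planned. It is not an arithmetic error. The cited beta applies to pre-post change within one arm. For the between-arm comparison at 0.59, power runs from 55% to 79% depending on losses, and no scenario without baseline adjustment reaches 80%. These figures rest on the assumptions listed in the working: two-sided 5%, a t-test on completers' change scores, equal SDs of change, and no mean PMCSMS change under Mindfulness. If the last fails because Mindfulness improves PMCSMS, power is lower.

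This should be fixed before Phase 1 is interpreted. Because Phase 2 is to be powered separately and no between-arm power is claimed, it does not call the design or the number recruited into question.

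**What to change.** Keep N = 90 and revise the sample-size paragraph to:

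- state alpha, sidedness and power as numbers, and say that 26 pairs supports pre-post change within one arm only;
- give the between-arm power as a range with its assumptions (57% at 27 per arm, about 70% at 36, 75% at 41, 79% at 45, for a difference of 0.59 SD of change), together with the minimum detectable differences at 80% power (about 0.67 SD at 36 per arm and 0.78 SD at 27);
- declare the Phase 1 between-arm result an estimate reported with a 95% confidence interval, so that a non-significant group-by-time test is not read as absence of preliminary efficacy when the larger trial is decided.

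The cost is one paragraph of text, with no extra participants and no change to design or analysis. The downside is that the stated power looks less favourable.

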### Study design

The Phase 1 trial is a block randomized, controlled, parallel group, two arm, assessor-blinded trial with a 1:1 allocation. Participants will be randomly assigned to either the Education and Self-Management Strategies or the Mindfulness Skills groups. The allocation sequence is determined using the random function in Microsoft Excel by the study coordinators prior to recruitment. The study coordinators will screen, consent, enroll, and assign participants to their study identity numbers. Qualitative assessment of *N* = 20 patients from the Education and Self-Management group will be purposively (i.e., subjectively) sampled to attain a heterogeneous subset of patients. Qualitative information will be combined with quantitative to permit a more thorough understanding of the outcomes and to aid in further program refinement before undertaking the Phase 2 full-scale RCT. This study design is summarized in COSORT flow diagram presented in Figure 1.

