#### Feasibility measures (Education and Self-Management group only; Objective 1)

(i)Recruitment (percentage of eligible participants that consented); retention (percentage of consented participants that completed the study); and adherence rates (percentage of sessions attended and outcome measures completed)(ii)Standard Session Feedback Form: this 5-item patient reported outcome measure (PROM) was created by our group, and uses a 5 point Likert scale to measure the utility of content/strategies, amount of content, barriers to application, and any changes/benefits noticed from applying the strategies.(iii)Exit interview: a semi-structured, qualitative interview comprising open-ended questions followed by probes. The interview probes pros/cons of intervention design and impact of the intervention on health and symptom self-management. Probes are based on the Workgroup for Intervention Development and Evaluation Research (WIDER) recommendations regarding content, format, delivery, timing issues and personnel (84). The interview will also contain probes for impact on health, health-related actions, including self-management of Long-COVID symptoms and health care visits.

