#### Efficacy measures (Objective 2)

All primary and secondary outcomes are PROMs. Table 3 summarizes the timeline of the outcome measure collection.

(i)Primary outcome:

Perceived Medical Condition Self-Management Scale (85) (PMCSMS). An 8 item tool using a 6-point scale to measure confidence to self-manage symptoms, with strong validity and reliability (85, 86), and associated with high treatment adherence and beneficial outcomes (85).

(ii)Secondary outcomes:

Utilization of Healthcare Services Questionnaire. This tool was created by our group to measure past and planned healthcare-related visits.Depression, Anxiety and Stress Scale (DASS-21 (87)). A 21-item tool that uses a 4-point scale to measure stress, depression and anxiety symptoms.Quality of Life Enjoyment and Satisfaction Questionnaire – Short Form (Q-LES-Q-SF (88)). A 16-time tool that uses a 5-point scale to measure quality of life and degree of enjoyment and satisfaction experienced by participants in various areas of daily living.Adapted Illness Intrusiveness Rating (AIIR (89, 90)). A 13-item scale using a 7-point scale to measure intrusiveness of symptoms in daily life.Life Orientation Test – Revised (LOT-R) (91). A 10-item tool using a 5-point scale to measure dispositional optimism.International Physical Activity Questionnaire (IPAC) (92). An 8-item tool to measure engagement in physical activity.

(iii)Control/Moderator variables

Brief COPE (93). A 28-item tool using a 4-point scale to measure ways of coping with stress in life.Somatic Symptom Scale – 8 (SSS-8 (94)). An 8-item tool using a 5-point scale to measure of somatic symptom burden.Multi-dimensional Health-Related Locus of Control (MHLC (95)). An 18-item tool to measure the locus of control for health-related behaviors.

**Table 3 tab3:** Summary and timeline of outcome measure collection.

Timeline		Outcome category	Outcome measures
Pre-intervention	Week 0; prior to first session	Feasibility (Objective 1)	Recruitment rate
		Efficacy (Objective 2)	Perceived Medical Condition Self-Management Scale Utilization of Healthcare Services Questionnaire Depression, Anxiety and Stress Scale Quality of Life Enjoyment and Satisfaction Questionnaire – Short Form Adapted Illness Intrusiveness Rating Brief COPE and Life Orientation test Somatic Symptom Scale Multi-dimensional Health-Related Locus of Control International Physical Activity Questionnaire

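### As described, the coordinators who generate the allocation list also decide entry, and the assessor-blinded label does not protect the self-reported efficacy outcomes

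*Protocol article*

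**What the plan says.** Two adjacent sentences of the protocol article, under Study design, assign the tasks around randomisation:

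- Generation: "The allocation sequence is determined using the random function in Microsoft Excel by the study coordinators prior to recruitment".
- Entry: "The study coordinators will screen, consent, enroll, and assign participants to their study identity numbers".

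The same section calls Phase 1 a "block randomized, controlled, parallel group, two arm, assessor-blinded trial with a 1:1 allocation". It gives no block size.

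Under Participants, one inclusion criterion is to "self-report experiencing 3 or more persisting symptoms from 2 or more categories of mood, cognitive and somatic domains".

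On outcomes, Efficacy measures (Objective 2) states: "All primary and secondary outcomes are PROMs". The primary one, the PMCSMS, is described as "An 8 item tool using a 6-point scale to measure confidence to self-manage symptoms".

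**The concern.** Concealment requires that whoever decides on entry cannot know which arm comes next. Here one role makes the list in advance and then screens and consents. If the person enrolling can see the list, the next assignment could influence how a borderline symptom report is judged, how the consent conversation goes, or when a candidate is entered. No misconduct need be assumed; foreknowledge is itself the weakness. Differences between arms that arise this way are part of the sample from the start, and adjustment can deal only with those that were measured.

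The second issue is the blinding claim. A reader of the trial report would take assessor-blinded to mean that the people scoring the outcomes did not know the arm. For these outcomes the scorer is the participant, who does know it.

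Both issues bear on decisions. Phase 1 compares the arms on efficacy, its results set the power analysis for Phase 2, and Phase 2 is conditional on preliminary efficacy being seen.

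**Working it through.** The point rests mainly on setting statements side by side. The arithmetic at the end shows only why no size is given.

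**1. Who does what (Study design)**

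| Task | Role named |
|---|---|
| Generate the sequence, before recruitment | Study coordinators |
| Screen | Study coordinators |
| Obtain consent | Study coordinators |
| Enrol | Study coordinators |
| Issue study numbers | Study coordinators |

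No other role appears at any step. This is a positive statement of responsibilities. Followed as written, it does not separate generation from enrolment.

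**2. Is there room for judgement at entry? (Participants)**

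Yes. The symptom criterion depends on self-report and on sorting symptoms into domains. The exclusion for major neurological or psychiatric conditions is introduced by examples, so it also needs interpretation. The proof-of-infection and age criteria leave little room.

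**3. Who rates the outcomes?**

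- Primary and secondary efficacy outcomes: the participant, in every case.
- Does the participant know the arm? Tables 1 and 2 show eight weekly sessions with openly different content, and nowhere does the article describe participants as blinded.
- Outcomes that are not self-ratings: the recruitment, retention and adherence rates. These belong to the feasibility measures, which are headed as covering the Education arm only, and they are summarised descriptively. They give assessor blinding no between-arm comparison to protect.

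**4. Where would a bias go?**

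- Efficacy analyzes: a group-by-time comparison on the PMCSMS, adjusted for acute COVID-19 severity and time since diagnosis.
- Aims and hypotheses: Phase 1 is to give the effect size, and Phase 2 is powered from Phase 1 results.
- Ethics and dissemination: the larger trial follows if preliminary efficacy is observed.

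A distorted Phase 1 contrast would therefore pass into both the go decision and the Phase 2 sample size.

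**5. Can the size be computed?**

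No. It would need the enrolling staff's actual access to the list, their use of it, and its effect on prognosis. The article gives none of these. Two apparent shortcuts fail:

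- *Scaling by the planning effect of 0.59.* Participants ties this value to paired tests and 26 pairs. Assuming two-sided alpha 0.05 and 80% power, the normal approximation is ((1.960 + 0.842)/0.59)² = 22.5, or 23 pairs. The exact paired t-test needs 25, and 26 pairs give 82.4% power. The stated 26 is thus reproduced to within one pair as a within-person calculation. A prognostic difference between arms is on another scale and cannot be expressed as a share of 0.59.
- *Comparing certain knowledge with a coin toss.* The trial is block randomised. Even with a hidden list, someone who knows past allocations and the block size guesses better than 50%. For an assumed block of 2, the expected share correct is (0.5 + 1)/2 = 75%. For an assumed block of 4 it is (0.5 + 2/3 + 2/3 + 1)/4 = 71%. Assumed blocks of 6, 8 and 10 give 68%, 67% and 65%.

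No sample size, power or alpha figure in the article depends on this point.

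**The case against.** The strongest reply is that the article does not say allocation is unconcealed. A reader might infer that coordinators keep the list beside them, know every next assignment, and issue study numbers that are keyed to it. The text supports none of these as fact. It says participants are assigned to identity numbers, not to arms. It speaks of coordinators in the plural, so different people may do the two jobs. Envelopes, a locked file or timed release are details that an article may leave to the full protocol. This stands, and it limits the claim to what the article describes: generation and enrolment lie with one role, so concealment is not shown. It does not remove the point, because the article goes beyond silence and places both tasks with the same role.

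A second reply is that the analysis offers some protection. The PMCSMS is measured before treatment, and two covariates are controlled. That deals with imbalance in those measured variables, so it would be wrong to say that analysis can do nothing. It does not deal with unmeasured prognosis or willingness to engage.

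Third, participants cannot be blinded to a behavioural programme, and confidence to self-manage is properly self-reported. The comparator is an active programme with the same number and length of remote sessions, which should narrow differences in expectation. All of this is fair. The fault lies in the label, not in the choice of outcomes or comparator.

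Fourth, Phase 1 is largely about feasibility, and the feasibility measures need no between-arm contrast. True, but the article also gives Phase 1 a comparative efficacy analysis and a gatekeeping role.

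**Conclusion.** The concern holds in a limited form. As described, one role generates the sequence before recruitment and then controls entry. Allocation is therefore not shown to be concealed from those who decide entry, where part of eligibility rests on self-report. The assessor-blinded label gives no protection to any primary or secondary efficacy outcome.

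The first conclusion assumes that the article describes the division of work correctly; if the full protocol separates the tasks between people and restricts access to the list, the remedy is to say so. The second does not depend on how coordinators divide their work. It follows from self-reported outcomes and openly different programmes.

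No size can be attached to any bias. The documents do not support the stronger readings that every assignment is known in advance, that bias has occurred, or that it amounts to some fraction of the planning effect. Nor does the blinding point extend to the recruitment, retention and adherence rates.

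**What to change.** 1. For remaining Phase 1 participants and for all of Phase 2, have an existing team member who does not recruit generate and hold the list. Coordinators should not have access to it.
2. Release each assignment only after eligibility, consent and baseline questionnaires are complete. Table 3 times baseline only against the first session, so the link to allocation should be written down.
3. Use varying block sizes that are not disclosed to recruiting staff, so that past allocations reveal less.
4. Report how many participants were enrolled before the change.
5. Replace the assessor-blinded label with a statement that participants and therapists are unblinded and that the efficacy outcomes are self-reported. Claim a blinded analyst only if that is put in place, since the article mentions none. Do not describe the outcome questionnaires as online unless that is confirmed; the article says so only of the background questionnaire.

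The cost is a small amendment and some set-up time, with no added staff or visits. Recruitment is already under way, so participants already enrolled are not covered, which is why their number should be reported.
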